**Methodology**

Enrolment and randomization process:

Eligible pregnant mothers at a gestational period of <=30weeks will be approached for an informed, written consent for participation in the study. Eligible infants will be stratified as per gestational age, viz. <28 weeks and 28^0/7^-30^6/7^weeks. Those who satisfied the inclusion and exclusion criteria after admission to the neonatal unit will be enrolled in the trial and will be randomly allocated to either mask or prong group.

A second randomization would be done to continue same interface or allocate to rotating group if the infant continues to be on the nasal CPAP after 8 hours of starting CPAP. Those randomized to rotating group will be subjected to mask interface if on prongs and those on prongs will be subjected to mask and the other group would continue with the same interface as before (Figure). Allocation will be done by a web based random number sequence generator ([www.randomization.com](http://www.randomization.com)). Separate person who is not involved in the study will generate the random sequence. Randomization will be stratified for gestation <28 weeks and 28 to 30 weeks. Allocations will be concealed by placing the allocation sequence in opaque, tamper proof, sealed, serially numbered envelopes. The nature of the intervention will prevent us from blinding of the intervention from the investigators as well as the treating team. However, the statistician and the neonatologist reviewing nasal injury images will be blinded from the study allocation details. Further attempts will be made to minimize the bias by maintaining a strict study protocol.

Gestational age will be calculated primarily based on mothers last menstrual period (LMP). In cases where LMP is unreliable, either an early dating scan or clinical postnatal assessment by new ballard score will be used to calculate the gestational age. Baseline demographic and clinical details such as antenatal steroids, evidence of chorioamnionitis, age at first surfactant, and clinical or echocardiographic evidence of patent ductus arteriosus, severity of illness and severity of respiratory distress [Silverman-Anderson score ^(20)^] will be recorded in a structured case record form. Neonates with onset of respiratory distress in the delivery room will be transferred to the NICU on a T piece device (Neopuff). The duration from birth to onset of intervention and duration of use of T piece will be recorded. The study intervention will start once the study subject is admitted to the NICU.
Interventions**:**

- **CPAP Nasal Mask Group**: The neonate will be given CPAP support by using appropriate sized Drager mask till CPAP is weaned off. The size of the mask chosen will be as per the manufacturer’s instructions.
- **CPAP Nasal Prongs Group**: The appropriate sized Hudson prongs as per the manufacturer’s instructions will be used for providing CPAP. The prongs will be continued.
- **Rotating group (Mask with Prongs and vice versa)**: The appropriate sized Drager mask and Hudson prongs will be rotated every 8 hourly (each nursing shift) for delivering CPAP. Care will be taken during these changes to minimize the duration of off-CPAP period.

Heating and humidification of gases: The gas delivered in both the devices was heated and humidified to attain a gas temperature of 37 degree C at the level of the nostrils. The humidifier used in both the groups had a flow-based servo-humidification control mechanism to ensure appropriate humidification. Protocol for titration, weaning and removal of CPAP is given in figure 1.

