**MATERIAL & METHODS**

Study site:

NICU, Fernandez Hospital, Hyderabad.

Study design:

A Prospective, Randomized, Comparative study.

Sample size with justification:

Assuming an incidence of nasal injury of 50% among the control group at the removal of CPAP from literature review and previous study from our center^(2-6)^. Assuming three group comparisons with an effect size of 30% with 80% power, alpha error of 5% the sample size calculated is 48 in each group and assuming an attrition rate of 10% we need 55 neonates in each group. Sample size was estimated by using Compare k Proportions: 1- way ANOVA Pairwise test ([www.powerandsamplesize.com](http://www.powerandsamplesize.com)). We will enroll patients till a minimum of 55 infants are enrolled in each group.

Time frame:

From september 2016 to march 2018.

Study population

Neonates admitted in NICU for respiratory distress

Inclusion criteria

- All inborn neonates <=30 weeks of gestation and
- Developed respiratory distress (presence of at least two out of three signs: tachypnea > 60/min, intercostal retractions, and expiratory grunt) within 6 hours of life.

Exclusion criteria

- Patients who have Perinatal depression (5 minute Apgar score of ≤3),
- Patients with Life threatening congenital malformations such as congenital diaphragmatic hernia, and trachea-esophageal fistula, other malformations that would prevent from establishing CPAP due to the anatomical defect such as Pierre-Robinson syndrome and choanal atresia
- Conditions where CPAP would be contraindicated such as neonates with poor spontaneous respiratory efforts or apnea, worsening shock, suspected or proven persistent pulmonary hypertension of newborn, severe metabolic acidosis (pH<7.2 with base deficit > -10), severe respiratory acidosis (pH<7.2 with PaCO2>55mmHg) and massive pulmonary hemorrhage

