**OUTCOMES MEASURED**

Six hours after the removal of nCPAP, infants will be assessed for nasal injury (Table 1) and digital photographs will be taken that will be reviewed by a senior neonatologist blinded to the study group allocation. Incidence and severity of nasal injury is the primary outcome of the study. Bedside subjective assessment of nasal injury will also be done by one of research assistant and this included; a) dilation of nares, b) columella indentation or excoriation, c) notching on the bridge of nose, d) altered shape of nose and e) redness /indentation/bleeding/excoriation of any area of nose.

The secondary outcomes of the study includes nCPAP failure, duration of nCPAP, duration of oxygen, culture positive sepsis, BPD, Intraventricular haemorrhages (IVH) grade ≥ 3. cystic periventricular leukomalacia (PVL), retinopathy of prematurity and mortality. Data will be collected until death or discharge from the hospital.

**Figure 1:** Clinical trial protocol for titration, weaning and removal of CPAP

[figure not shown]

Note: Titration will be done primarily based on clinical features and pulse oxygen saturation; arterial blood gas and chest X ray will be used for decision making wherever available

* <6 and >8 posterior intercostals spaces is defined as under and over inflation respectively, ^£^ICR: Intercostal Retractions

**Weaning of CPAP**: Weaning from CPAP will be attempted if the infant will have good respiratory efforts and will be free of apneas and bradycardia in the past 24 hours and if one or more of the following will be present:

1. Stable or decreasing oxygen requirement over the past 12 hours
2. Chest wall hyperinflated* (either clinically or in a Chest X ray) with absence of retractions and a pulmonary air leak ruled out.

Note: If the infant did not tolerate the decrease in CPAP, as judged by an increase in oxygen requirement by 15% more than that in the preceding 12 hours, the CPAP pressure will be again increased by1 cm of H_2_O.

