**Monitoring chart for nasal injury**

| **Nasal injury** | **Score** | | | | | | | | | | |
| --- | --- | --- | --- | --- | --- | --- | --- | --- | --- | --- | --- |
|  | **Day 1** | **Day 2** | **Day 3** | **Day 4** | **Day 5** | **Day 6** | **Day 7** | **Day 14** | **Day 21** | **Day 28** | **Discharge** |
| **Tip of Nose** |  |  |  |  |  |  |  |  |  |  |  |
|  |  |  |  |  |  |  |  |  |  |  |  |
| **Nasal Septum** |  |  |  |  |  |  |  |  |  |  |  |
|  |  |  |  |  |  |  |  |  |  |  |  |
| **Nostrils** |  |  |  |  |  |  |  |  |  |  |  |
|  |  |  |  |  |  |  |  |  |  |  |  |
| **Nose Shape** |  |  |  |  |  |  |  |  |  |  |  |
|  |  |  |  |  |  |  |  |  |  |  |  |
| **Bridge of the nose** |  |  |  |  |  |  |  |  |  |  |  |
| **Upper lip** |  |  |  |  |  |  |  |  |  |  |  |
| **Total score** |  |  |  |  |  |  |  |  |  |  |  |

| PATIENT END | | | | | MACHINE END | | | | | Interface and settings | | |
| --- | --- | --- | --- | --- | --- | --- | --- | --- | --- | --- | --- | --- |
|  | Distance between cannula& interface-2mm | Nasal skin blanched | Columella/ septal excoriation | Oral/nasal suction done | Bubble present | Temperature normal | Tubings below patient level | Flow rate  5-8 L/min | Water level (Humidifier& Container) | Mask or prong | FiO2 | PEEP |
| 0800 |  |  |  |  |  |  |  |  |  |  |  |  |
| 1200 |  |  |  |  |  |  |  |  |  |  |  |  |
| 1600 |  |  |  |  |  |  |  |  |  |  |  |  |
| 2000 |  |  |  |  |  |  |  |  |  |  |  |  |
| 0000 |  |  |  |  |  |  |  |  |  |  |  |  |
| 0400 |  |  |  |  |  |  |  |  |  |  |  |  |
| Signature |  |  |  |  |  |  |  |  |  |  |  |  |

CPAP Monitoring chart

Name of the baby: MR No: Enrolment No: Group allocated:

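### No Table 1 nasal score is fixed at the second randomisation (8 h of CPAP), so injury already present then cannot be separated from later injury or adjusted for when rotation is compared with continuing

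*Protocol*

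**What the plan says.** Under Methodology, infants are first randomised to mask or prongs. A second randomisation is then made to continue the same interface or to "allocate to rotating group if the infant continues to be on the nasal CPAP after 8 hours of starting CPAP". Infants allocated to rotation change interface at that point, and the interventions section has them change again every 8 hours.

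Under Outcomes measured, "Incidence and severity of nasal injury is the primary outcome of the study", and the assessment is made six hours after nCPAP comes off. On the Table 1 scale a total of 0 is no injury and 1 to 4 is mild injury, so redness at a single site is enough to count. Nothing excludes or adjusts for injury present at the second randomisation.

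In Annexure 1, the form headed "Monitoring chart for nasal injury" has columns for Days 1 to 7, 14, 21, 28 and discharge. It has no column for hour 8, and Day 1 has no stated hour. The enrolment form asks for the respiratory severity score at randomisation but for no nasal score then, and its item for the maximum nasal injury score has no start time. A separate 4-hourly CPAP chart has columns for blanching and for columella or septal excoriation.

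**The concern.** The trial's aim is to learn whether rotation lowers the incidence of nasal injury compared with one interface throughout. For that comparison, baseline is the second randomisation. Allocation at 8 h cannot have prevented an injury that already existed at 8 h. If that injury is still there at the final assessment, it is an event in whichever group the infant joined.

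Without a baseline on the outcome scale, the trial cannot say how much of the final injury arose after allocation. It also cannot adjust for a chance difference in early injury between the groups. An analysis plan cannot repair this later, because a score not taken before the second envelope is opened cannot be recreated.

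**Working it through.** **Inputs from the protocol (Sample size with justification).** The control rate is given as "Assuming an incidence of nasal injury of 50% among the control group at the removal of CPAP". The calculation is stated as "effect size of 30% with 80% power, alpha error of 5% the sample size calculated is 48 in each group", by the method "Compare k Proportions: 1- way ANOVA Pairwise test".

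**Reproducing 48 per group.** Take 50% versus 20%, unpooled variance, and two-sided alpha 0.05/3 for three pairwise comparisons. Then z(1 − 0.05/6) = 2.394 and z(0.80) = 0.842.

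n = [0.5×0.5 + 0.2×0.8] × ((2.394 + 0.842)/0.30)² = 47.69, which rounds up to 48.

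The stated figure is reproduced. The 30% is therefore an absolute difference, and the planned ratio of rates is 0.20/0.50 = 0.4.

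**Illustration of possible dilution.** Let b be the share of all infants whose injury is present at 8 h and persists to the final assessment. The protocol gives no value for b, so the values below are assumptions. Control stays at 50%, and rotation is taken to act only on later injury, with ratio 0.4:

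- rotation rate p = b + 0.4 × (0.50 − b)
- power at 48 per group = Φ( (0.50 − p) / √{[0.25 + p(1 − p)]/48} − 2.394 )

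| b (assumed) | Share of the 50% control injuries | p | Difference | Power at 48 | n per group for 80% |
|---|---|---|---|---|---|
| 0% | 0% | 20% | 30 points | 80% | 48 |
| 2.5% | 5% | 21.5% | 28.5 points | 74% | 54 |
| 5% | 10% | 23% | 27 points | 68% | 62 |
| 10% | 20% | 26% | 24 points | 54% | 81 |
| 15% | 30% | 29% | 21 points | 41% | 109 |

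For b = 5%: p = 0.05 + 0.4×0.45 = 0.23. The standard error is √(0.4271/48) = 0.0943, and 0.27/0.0943 − 2.394 = 0.468, so power is 0.68.

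**Chance imbalance.** With 48 per group, the 95% range for a chance difference in early injury is ±1.96 × √(2b(1 − b)/48). This gives about ±9 points for b = 5% and ±12 points for b = 10%. Randomisation is stratified by gestation only, so nothing planned removes this noise.

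**What the existing records could supply.** The Day 1 score is on the right scale but is not timed against the first switch. The 4-hourly checks are frequent enough, but they cover only blanching and columella or septal excoriation. They do not give the Table 1 scores for tip, nostrils, shape, bridge and lip. They are a partial proxy.

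**The case against.** The strongest reply is that the first 8 hours are not a run-in. Rotation is 8-hourly, so any rotated infant spends the first period on one interface, and injury arising then is part of the strategy's result. This is a fair reading, and it means that counting all injury is a legitimate primary outcome. It does not supply a baseline for the comparison randomised at 8 h.

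A reader might infer that the planned 30-point effect is diluted, or that the trial is underpowered for this reason. The protocol does not support that. It does not say whether the 30 points already allow for early injury. Early injury counts only if it lasts through the CPAP course and six hours beyond, and redness may resolve. An injured nose might also heal under rotation, and severity is part of the outcome. The trials summarised in the literature review link injury to duration of CPAP, which does not favour the upper end of the assumed range.

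A reader might also infer bias. That fails too: allocation at 8 h balances earlier injury in expectation within each starting interface.

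Finally, an 8 h score follows the mask-or-prong randomisation and may partly reflect it. Adjusting mask versus prongs for it could remove part of that effect. This objection stands and limits the remedy.

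**Conclusion.** The point holds in a limited form. The protocol fixes no Table 1 score at the second randomisation, so early persisting injury can be neither separated nor adjusted for on the primary outcome scale. The loss is in precision and interpretability.

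Whether there is any dilution, and how much, cannot be known from the protocol. The power figures of 68% and 54% rest on three assumptions: early persisting injury in 5% or 10% of infants, no effect of rotation on that injury, and a planned effect that does not already allow for it. If early persisting injury is near zero, power stays at about 80%. The change is worth making because it is cheap and cannot be made afterwards.

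**What to change.** - State that the Day 1 Table 1 score is taken at 8 h of CPAP, immediately before the second envelope is opened. It is then made without knowledge of the second allocation.
- Use this score as a baseline covariate only for rotate versus continue, within or stratified by starting interface. Do not use it for mask versus prongs.
- Keep the primary outcome as it is. Add injury that is new or worse than at 8 h as a supportive analysis.

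The cost is one timing instruction on an existing chart column, one covariate and one supportive analysis. There are two downsides. Staff lose freedom over when the Day 1 score is made. The baseline score is also made at the bedside by staff who know the starting interface, whereas the outcome photographs are reviewed blind.

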**OUTCOMES MEASURED**

Six hours after the removal of nCPAP, infants will be assessed for nasal injury (Table 1) and digital photographs will be taken that will be reviewed by a senior neonatologist blinded to the study group allocation. Incidence and severity of nasal injury is the primary outcome of the study. Bedside subjective assessment of nasal injury will also be done by one of research assistant and this included; a) dilation of nares, b) columella indentation or excoriation, c) notching on the bridge of nose, d) altered shape of nose and e) redness /indentation/bleeding/excoriation of any area of nose.

The secondary outcomes of the study includes nCPAP failure, duration of nCPAP, duration of oxygen, culture positive sepsis, BPD, Intraventricular haemorrhages (IVH) grade ≥ 3. cystic periventricular leukomalacia (PVL), retinopathy of prematurity and mortality. Data will be collected until death or discharge from the hospital.

**Figure 1:** Clinical trial protocol for titration, weaning and removal of CPAP

[figure not shown]

Note: Titration will be done primarily based on clinical features and pulse oxygen saturation; arterial blood gas and chest X ray will be used for decision making wherever available

* <6 and >8 posterior intercostals spaces is defined as under and over inflation respectively, ^£^ICR: Intercostal Retractions

**Weaning of CPAP**: Weaning from CPAP will be attempted if the infant will have good respiratory efforts and will be free of apneas and bradycardia in the past 24 hours and if one or more of the following will be present:

1. Stable or decreasing oxygen requirement over the past 12 hours
2. Chest wall hyperinflated* (either clinically or in a Chest X ray) with absence of retractions and a pulmonary air leak ruled out.

Note: If the infant did not tolerate the decrease in CPAP, as judged by an increase in oxygen requirement by 15% more than that in the preceding 12 hours, the CPAP pressure will be again increased by1 cm of H_2_O.

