Sorabh Goel, Jayashree Mondkar et al 2015 ^(18)^ compared the effectiveness of nasal continuous positive airway pressure delivered by Nasal mask vs Nasal prongs with nasal trauma as secondary outcome. They conducted a randomized controlled, open label, trial at tertiary care level III neonatal unit.118 preterm infants-gestational age (27-34 weeks) requiring nasal continuous positive airway pressure as a primary mode for respiratory distress were included . 61 received nCPAP with nasal Mask as interface and 57 received nCPAP with nasal Prong as interface. Nasal continuous positive airway pressure failure occurred in 8 (13%) of Mask group and 14 (25%) of Prongs group but was statistically not significant (RR 0.53, 95% CI 0.24-1.17) (P = 0.15). The rate of pulmonary interstitial emphysema was significantly less in the Mask group (4.9% vs. 17.5%; RR 0.28, 95% CI 0.08-0.96; P = 0.03). Incidence of moderate nasal trauma (6.5% vs 21%) (P=0.03) and overall nasal trauma (36% vs 58%) (P=0.02) were significantly lower in mask group than in the prongs group.

Aparna Chandrasekaran et al ^(19)^ compared nasal mask vs nasal prong as an interface to deliver nCPAP with FiO2 requirement at 6, 12 and 24 h of CPAP initiation as primary outcome and nasal injury as secondary outcome. they conducted a randomized controlled trial at teaching hospital in new delhi from April 2012 to June 2013. 72 neonates were enrolled in the study —37 were assigned to the nasal mask group and 35 to the nasal prongs group. They found that FiO2 requirement comparable between two groups. The incidence of any grade of nasal trauma during the first 72 h was comparable between the groups (RR 1.07, 95% CI 0.84–1.35, p = .59). The incidence of severe—grade II/III— nasal trauma was, however, significantly lower in the mask group (0 vs. 31%; p < .001). authors concluded that Nasal masks appear to be as efficacious as binasal prongs in providing CPAP with Masks being associated with lower risk of severe nasal trauma.

From The above review of literature it seems both short binasal prongs and nasal mask are equally effective in delivering nCPAP but the measure concern is nasal injury that varies from mild to severe enough requiring corrective surgery, so we are planning to compare whether rotation of nasal interfaces will decrease the incidence of nasal injury as compared to nasal mask or nasal prong alone in neonates on nasal CPAP.

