**AIMS & OBJECTIVES**

AIM

To know whether rotation of nasal interfaces will decrease the incidence of nasal injury as compared to nasal mask or nasal prong alone in neonates on nasal CPAP.

OBJECTIVES

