**Primary objective**

1. To identify the incidence and severity of nasal injury at removal of CPAP in all the three groups (i.e. rotation group, mask continue group, prong continue group) based on the objective scoring and a subjective assessment.

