**First Randomization**

**Second Randomization**

**Statistical analysis**

Categorical outcome variables will be analysed by Chi square test with continuity correction or Fisher’s exact test. Normal distributed independent variables will be compared by repeated measures ANOVA test whereas a non-parametric test (Mann-Whitney U) will be used for variables with a skewed distribution. An Intention to treat analysis will be done (ITT). All analysis will be done using IBM SPSS version 21 and Microsoft Excel. A P value of less than 0.05 will be considered significant.

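### Incidence and severity of nasal injury are both named primary at P<0.05 with no rule for which decides, although aim, title and sample size rest on incidence alone

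*Protocol*

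**What the plan says.** Two places in the protocol define what is primary, and both name a pair. The primary objective reads: "To identify the incidence and severity of nasal injury at removal of CPAP in all the three groups". The Outcomes Measured section reads: "Incidence and severity of nasal injury is the primary outcome of the study".

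Three places concern incidence alone. The aim is "To know whether rotation of nasal interfaces will decrease the incidence of nasal injury as compared to nasal mask or nasal prong alone". The study title in Annexure 1 asks the same question. The sample size begins: "Assuming an incidence of nasal injury of 50% among the control group at the removal of CPAP", and continues with an "effect size of 30% with 80% power, alpha error of 5% the sample size calculated is 48 in each group".

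Both measures come from one instrument. Table 1 scores six areas of the nose, and the Scoring list grades the total as none (0), mild (1-4), moderate (5-6) or severe (7 or more). The protocol does not define incidence separately. The natural reading is a score of 1 or more against 0.

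The Statistical analysis section gives general rules by type of variable, among them "Categorical outcome variables will be analysed by Chi square test with continuity correction or Fisher’s exact test", and one threshold: "A P value of less than 0.05 will be considered significant". It does not rank incidence and severity, require both, divide alpha between them or describe a single ordinal analysis.

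**The concern.** A primary outcome should fix, before data are seen, which result decides the trial. Here two measures carry that label and only one was used to size the study. If incidence is null and severity is significant, or the reverse, the text does not stop the significant one from being reported as the primary result. This has two consequences: the false-positive rate for a primary claim rises above 5%, and the measure that carries the conclusion can be chosen afterwards.

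Disagreement between the two is plausible. In the protocol's Nasal Interface section, a 72-infant mask-versus-prongs trial found no difference in any-grade trauma (RR 1.07, 95% CI 0.84-1.35, p = .59) but grade II/III trauma of 0 vs 31% (p < .001).

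The issue is separate from multiplicity over the three pairs of groups. It would remain with a single three-group test for each measure.

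**Working it through.** **1. What the stated sample size covers.** Inputs from the sample size paragraph: p1 = 0.50; effect 30%, read as absolute, so p2 = 0.20; power 80%; alpha 5%, taken as two-sided; pairwise comparison of three groups.

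n = [p1(1−p1) + p2(1−p2)] × [(z(1−0.05/(2×3)) + z(0.80)) / (p1−p2)]²

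= (0.25 + 0.16) × [(2.394 + 0.842) / 0.30]² = 47.7, so 48 per group.

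This reproduces the plan's figure. The same formula gives 36 without adjustment and 44 with adjustment for two pairs. Attrition: 48/0.9 = 53.3, so 54, against the stated 55. The Bonferroni factor therefore covers the three pairs for incidence. The whole 5% is spent there, and severity has neither alpha nor sizing.

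**2. Ceiling for two measures at 0.05.** If they were independent: 1 − 0.95² = 9.75%. They are not independent, because incidence is the lowest cut of the graded score, so the true figure is lower.

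**3. Simulation of the overlap.** Three groups of 48, 50% injured in every group (no true difference), one three-group test per measure at 0.05, 8,000 runs per scenario. The protocol gives no severity distribution, so splits among injured infants were assumed: 70/20/10, 50/30/20 and 40/30/30% mild/moderate/severe. The protocol also does not say how severity is to be tested, so three forms were tried.

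| Second primary measure, beside incidence | Chance that either is significant | Repeat simulation, same design |
|---|---|---|
| Four-level grade, chi-square | 8.2-8.5% | 7.9-8.7% |
| Moderate-to-severe injury, chi-square | 8.9-9.7% | 9.1-9.4% |
| Grade, rank test | 6.7-7.1% | 6.6-7.0% |

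The simulation error is about √(0.085 × 0.915 / 8000) = 0.3 percentage points. The highest value, 9.7%, came from the scenario in which the incidence test alone came out at 5.8% (5.3% in the other two, under the same null), so it is partly noise. Every variant exceeds 5%; about 7 to 9% is a fair summary.

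**4. Can the two measures disagree?** For the 72-infant trial, 31% of 35 is about 11 infants (count assumed). Fisher's exact test of 0/37 against 11/35 gives p = 0.00014, consistent with the reported p < .001, beside p = .59 for any grade. In the other mask-versus-prongs trial in the same section that reports both, the measures agree: overall trauma 36% vs 58% (P = 0.02) and moderate trauma 6.5% vs 21% (P = 0.03).

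**5. Price of the alternatives.** With incidence as sole primary, or a fixed order starting with incidence, 48 (55) per group stands. With alpha split equally, 0.025 each and still three pairs, z(1−0.05/12) = 2.638 replaces 2.394: 0.41 × [(2.638 + 0.842)/0.30]² = 55.2, so 56 per group, and 56/0.9 = 62.2, so 63 with attrition. At 48 per group, power for 50% vs 20% under that split falls from 80% to about 73%.

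**The case against.** The strongest reply is that there is only one outcome. The sentence is in the singular, both measures come from one Table 1 total, and incidence is that total's lowest cut. Aim, title and sizing all point to incidence, so the gap may be only a missing ranking word, and testing order is often left to a statistical analysis plan. Part of this stands. The protocol never says that either result alone would make the trial positive; that possibility follows from its silence. But no ordinal analysis is described, and the sizing is for a binary proportion, which does not fit a single graded outcome. Naming the primary outcome is the protocol's task, and here the wording conflicts with its own aim and sizing.

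Two stronger readings are tempting, and the documents do not support them.

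- A reader might infer that the two measures can give opposite answers. The cited trial shows a null result beside a strongly positive one, not effects in opposite directions, and another cited trial shows agreement. The example also compared mask with prongs without rotation, and its any-grade result covered the first 72 hours.
- A reader might add the three pairs of groups and infer an error rate in the mid-teens. Pairwise simulation can give 14-17% for either measure, against 8-9% for incidence alone. That contrast sets a continuity-corrected incidence test against an uncorrected severity test; uncorrected incidence alone already gives 12-13%. It also brings in the separate three-pair issue, although 48 per group reproduces only with Bonferroni over three pairs.

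It is also fair to say that with a rank test for severity the excess over 5% is only about 2 percentage points.

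**Conclusion.** The point holds as a badly fixed primary outcome of moderate consequence. Two measures are named primary under one P<0.05 rule, nothing says which decides, and only incidence has been sized. Tested side by side, they carry a chance of about 7 to 9% of at least one false-positive primary result, against 5% intended. That range assumes 48 per group, 50% incidence, one three-group test per measure and the severity splits listed above, and it moves with the way severity is tested. Conflicting conclusions are possible, as one cited trial shows, but they are not inevitable.

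**What to change.** In the Primary objective and Outcomes Measured sections, name incidence of nasal injury (Table 1 total score of 1 or more, assessed six hours after CPAP removal) as the single primary outcome. Make severity grade the first secondary outcome, formally tested at 5% only if the incidence comparison is significant, and otherwise reported with estimates and confidence intervals.

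This is a change of wording only: no extra infants or data, and 48 (55) per group remains valid. The real cost is that a difference in severity alone, such as the pattern in the cited 72-infant trial, would no longer be a confirmatory primary result. If the sponsor is unwilling to accept that, an equal alpha split is coherent but needs 63 instead of 55 per group (3 × 8 = 24 more infants) to keep 80% power for incidence. A single prespecified ordinal analysis would also resolve the ambiguity, but the sample size would have to be justified afresh for it.
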